#### Implementation

The researchers use a computer to generate two random sequences, allocated the eight community health centers in Baoshan District and six CHSs in Jing’an District, respectively, in a ratio of 1:1 into an intervention and a control group to receive CDSS intervention or usual care.

#### Allocation concealment mechanism

The allocation results of each community health center were told to the administrators by telephone. Each administrator only knows the result of his or her own site.

#### Blinding

The researchers, participants, and data analysts will not be blinded, but the participants will not be allowed to know the outcomes of this study.

### Interventions

#### Introduction

The intervention in this study is an AI-assisted CDSS on non-valvular AF management which was developed for this study in conjunction with Ping An Healthcare and Technology Co., Ltd. The CDSS was designed based on China’s latest AF treatment-related documents. It possesses the abilities to automatically evaluate the risk of stroke using CHADS_2_ score and CHADS_2_-VASc score and bleeding by HAS-BLED score, ORBIT score, and ATRIA score and provide initial treatment, follow-up, and dosage adjustment suggestions. It also contains the new functions of providing referral suggestions, anticoagulant instructions, and tips on the interaction between the selected anticoagulants and other drugs or food, assessing fall risk and balance using the Tinetti Scale and Self-rated Fall Risk Questionnaire (self-rated FRQ)), cognition by the Mini-Mental State Examination (MMSE), emotional and psychological disorders using the geriatrics depression scale-15 (GDS-15), and the confusion assessment method (CAM). It will only be used to provide evidence-based advice to physicians without any person-AI interaction and the final decisions will still be made by GPs. The Shenzhen Wang’an Computer Safety Checking & Measuring Technology Co., Ltd. examined the system security and the developers evaluated the stability and algorithm verification. The rationality of the decisions was checked by cardiological experts.

#### Preparation

Prior to be used, the CDSS will be embedded into the HIS of community health centers in the intervention group. The GPs will be trained in the use of the CDSS within the intervention group by developers from Ping An Healthcare and Technology Co.Ltd., and GPs of both groups will be trained in AF management by the researchers. After training, the training materials will be bound into a handbook and provided to the GPs for free.

#### Usage

After training, GPs in the intervention group can use the CDSS to manage patients with AF. It will capture the diagnosis code automatically after being linked with HIS, so when a patient is diagnosed as AF or atrial flutter, a pop-up reminder will show up. The interface of the CDSS will be presented after GPs click on the pop-up window. Referral indicators will be showed first to remind GPs of judging whether the patient needs to be referred to a superior hospital. The referral indications included immediate and general indicators [28]. The detail introductions are separated into initial and follow-up visit patients.

##### Initial patients

Initial patients is defined as the patients who see the doctor in community health centers for the first time due to AF and have not been treated with any anticoagulants. The management interface is shown in Fig. 1a. The management procedures are in order:
Electrocardiogram (ECG) and echocardiography as in Fig. 1b. GPs will need to choose the appropriate option according to the patient’s ECG and echocardiography. If the ventricular rate is faster than 100 beats per minute or slower than 60 beats per minute, or if echocardiography is unavailable, or if a valvular disorder is suggested, the CDSS will advise referring the patients to superior hospitals to first regulate the ventricular rate, check the echocardiography, or treat the valvular disorders.Those patients with ventricular rates ranging from 60 to 100 beats per minute and echocardiography reported as normal valvular function can continue with the CDSS. The anticoagulants, including warfarin and NOACs, and medical history including initial AF, Grave’s disease, cancer, recent stroke, and cardiovascular heart disease (CHD) are shown in Fig. 1b. If patients are taking such drugs, the CDSS will change to the follow-up interface. If the patients are diagnosed with any one of the diseases, the CDSS will advise referral.Laboratory findings are shown in Fig. 1b. The CDSS will autoload relevant and latest laboratory findings within the last 3 months recorded in HIS. The required parameters are systolic and diastolic pressure in mmHg, hemoglobin (HGB) in g/L, hematocrit (HCT) as a percentage, platelet count (PLT) in units 10 [9]/L, alanine aminotransferase (ALT) and aspartate aminotransferase (AST) both in U/L, total bilirubin (TBIL) in μmol/L, direct bilirubin (DBIL) in μmol/L, blood urea nitrogen (BUN) in mmol/L, serum creatinine (Scr) in μmol/L, glomerular filtration rate (eGFR) as ml/min/1.73 m^2^), activated partial thromboplastin time (APTT) and prothrombin time (PT) both per second, left atrial diameter (LAD), left ventricular end-diastolic (LVIDd) and left ventricular end-systolic (LVIDs) all in mm, left ventricular ejection fraction (LVEF) as %, free T3 (FT3) and free T4 (FT4), both as pmol/L, thyroid-stimulating hormone (TSH) in IU/ml, serum potassium (K) as mol/L and NT-proBNP in pg/ml. Missing information in HIS will be corrected by GPs asking the patients.Medical history and drugs are shown in Fig. 1b. Detailed medical history included the presence or otherwise of vascular disease, cirrhosis, dialysis-dependent renal disease or renal transplantation, hypertension, heart failure, diabetes, a major ischemic stroke within 2 weeks, bleeding, other hemorrhagic diseases, peptic ulcer, perioperative period, labile INR, excessive alcohol drinking, pregnancy, and undesired long-term anticoagulation. Current drugs include vitamin K antagonist (VKA), antiplatelet, and non-steroidal anti-inflammatory agents (NSAIDs).CGA as seen in Fig. 1a, where if necessary, GPs can choose one or more assessments for patients, including fall risk and balance, cognition, and emotional and psychological disorders.Finally, recommendations will be provided by the CDSS, including scores, risk levels, and suggestions on treatment, referral, and follow-up, according to the risk of stroke and bleeding (Fig. 2). If the assessment result of a patient is the need for anticoagulation, the CDSS will also provide the linkages of usage and cautions, instructions, and tips on the interaction between anticoagulants and other drugs or food to GPs (Fig. 2) [29].

**Fig. 1 Fig1:**
[figure not shown]
The interface of the CDSS for initial patients

**Fig. 2 Fig2:**
[figure not shown]
Example of suggestions for initial patients

##### Follow-up visit patients

The follow-up patient management interface is shown in Fig. 3a and the example of result assessment is seen in Fig. 3b. For those with a recent stroke or bleeding, the CDSS will advise referring the patients and for those without, patients treated with NOAC or with no anticoagulants will be selected for continual follow-up and patients treated with warfarin will be provided recommendations based on their recent INR values.

**Fig. 3 Fig3:**
[figure not shown]
The interface of CDSS for follow-up visit patients

### Outcomes

The primary outcome is the proportion of antithrombotic treatment prescriptions, in agreement with recommendations in the AF guidelines. It is defined as the agreement rate between the doctor’s anticoagulation prescriptions for newly diagnosed patients and the system’s recommendations, including prescribing anticoagulation drugs or recommending referral to superior hospitals for patients with anticoagulation indications, and refraining from anticoagulation for patients without such indications or with contraindications.

The safety outcomes, such as the incidence of bleeding events, all-cause mortality and in-patient events related to AF or AF complications will be reported. Referring to the Guideline of stroke prevention in Chinese patients with atrial fibrillation (2017), bleeding events are classified as minor and major bleeding [4].

The secondary outcomes contain seven items:
Frequency of consultation is defined as the average times of patients in each group seeking medical care due to AF in community health centers.The INR compliance rate in patients with warfarin is defined as the number of patients with AF treated with warfarin whose TTR values exceed 65%, but excluding those whose INR values exceed 5.0 or are less than 1.5 at least twice in 6 months, or exceed 8.0 at least once [30]. For this calculation, INR values within the initial 6 weeks will be deleted and no less than 6-month INR values should be included.Stroke morbidity during follow-up, including ischemic stroke and transient ischemic attack (TIA).Medication satisfaction of patients, assessed with the Chinese version of the patient satisfaction questionnaire (PSQ-18) [31].The GPs’ capability to manage AF, assessed using a self-administered questionnaire, “Knowledge-Attitude-Practice (KAP) questionnaire of community primary care physicians (PCPs) in anticoagulant therapy for non-valvular atrial fibrillation (NVAF) patients” [32], which was developed and validated by Delphi technique and the reliability and validity evaluation were confirmed by empirical research among GPs in Shanghai [33].Cost-benefit analysis. The costs mainly include the time and labor costs caused by the design, installation, and maintenance of the CDSS compared with the control group, the excess time and labor costs led by GPs using the auxiliary tool and the loss of productivity due to patients’ longer visit time caused by using the CDSS.The GPs’ acceptance of and rational and optimal advice on the CDSS. For this part, we plan to conduct semi-structured interviews

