### Settings and participants

The requirements for using the CDSS in community health centers are that their servers of the hospital information systems (HISs) are at least with eight-core central processing unit, 32 GB RAM, hard drive of 500 G, and operating system of Centos 7.2. Fourteen community health centers willing to participant in this study in Baoshan District and Jing’an District of Shanghai were recruited by researchers. Baoshan District and Jing’an District are in the suburb and urban area of Shanghai, respectively, so are geographically representative (Additional file 2).

The participants are GPs and patients with AF in the selected community health centers. For GPs, the inclusion criteria are that they work in GP consulting rooms or the AF special consulting rooms in their community health center, are willing to participate in the study, and can complete the pre-training on AF management and CDSS use. They will be excluded if they rarely use computers in their daily work, or cannot complete the whole study.

Patients will be included if they are 18 years old or older, diagnosed with any type of AF or atrial flutter (ICD-10 codes shown in Additional file 3) during a consultation or in medical history, registered with GP for at least 1 year, and are willing to participate in the study and sign the informed consent (Additional file 4). They will be excluded if they are diagnosed with end-stage disease such as advanced tumors, or their expected survival time is less than 1 year, or are unable to cooperate with the study due to illiteracy or dementia, or cannot continually consult in the registered community health centers in the next 1 year due to objective conditions such as moving, or with valvular AF or prosthetic valves, or are participating in other clinical trials related to AF, or are pregnant or breastfeeding. Subjects can reserve the right to drop out due to any reason or without reason and at any time during the study. If any incident happens to the subjects, such as death, disability, or dementia, they could withdraw from the study after applying by their legal representatives and evaluating by researchers. Subjects who are pregnant during the follow-up and plan to give birth will be considered as withdrawal.

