### Sample size

A previous study reported that 12.64% of patients with AF received appropriate anticoagulants in community health centers of Shanghai [34]. Intracluster correlation coefficient (ICC) was 0.02 [35], the power (1-β) was 90%, and the double-sided significance (α) was 0.05. In the pilot study, the proportion of appropriate anticoagulation increased to 28% in the intervention group, so we expected the proportion to be 28% in this study. Seven community health centers are in each group and we plan to enroll 30 patients from each community health center in the control group, meaning a sample size of 448, or 498 to allow for a 10% loss to follow-up.

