## Trial status

This publication is based on version 1.2 of the trial protocol dated Oct. 15, 2021. It is planned to enroll participants in Jan. 2022, and to follow up until Jan. 2023 (Fig. 5).

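### The primary outcome is defined for newly diagnosed patients only, but the 90% power holds only if all 448 evaluable patients with AF count towards it

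*Protocol article*

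**What the plan says.** The Outcomes section opens in general terms: "The primary outcome is the proportion of antithrombotic treatment prescriptions", in agreement with the AF guidelines. The next sentence gives the operative definition: the rate at which the doctor's "anticoagulation prescriptions for newly diagnosed patients" agree with what the system recommends. Agreement covers prescribing an anticoagulant or referring when one is indicated, and refraining when it is not indicated or is contraindicated. The article does not define newly diagnosed.

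The Settings and participants section admits adults "diagnosed with any type of AF or atrial flutter (ICD-10 codes shown in Additional file 3) during a consultation or in medical history", provided that they have been registered with the GP for at least a year. Current anticoagulant use is not an exclusion.

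The nearest defined group is in the Initial patients section: those who "see the doctor in community health centers for the first time due to AF and have not been treated with any anticoagulants". That section sends anyone already taking an anticoagulant to the follow-up interface. The Follow-up visit patients section covers people on a NOAC, on warfarin or on no anticoagulant.

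The Sample size section takes its control proportion of 12.64% from patients with AF in general and states that "we plan to enroll 30 patients from each community health center in the control group, meaning a sample size of 448", raised to 498 for 10% loss to follow-up. The Abstract calls the 498 patients with AF and gives the primary outcome without the restriction.

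**The concern.** Two populations are in play. The primary outcome belongs to a subset of those enrolled, while the sample size is built on all of them. An enrolled patient with long-standing AF who is already on treatment counts towards 498 but, under the stated definition, adds nothing to the primary analysis.

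Two things are at stake. If the definition is followed, the primary analysis has fewer patients than planned by an unknown amount, and a null result could reflect lack of power rather than lack of effect. If it is not followed, someone must decide later who counts. The Blinding section says that the trial is open and that the data analysts are not blinded, so that decision could be made with the data in view.

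**Working it through.** **Inputs, all from the Sample size section.** Control proportion p1 = 0.1264; intervention proportion p2 = 0.28; difference 0.1536; ICC 0.02; 7 centres per arm; 30 patients per control centre; two-sided alpha 0.05; power 90%; total 448, or 498 after loss to follow-up.

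**Intervention centre size.** The article does not state it, but it follows from the total: 448 − 7×30 = 238, and 238/7 = 34.

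**Formula.** For an arm with m patients per centre, variance = p(1−p)[1 + (m−1)×0.02]/(7m). Power = Φ(0.1536/√(v1+v2) − 1.96).

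**Reproducing the plan's figure.**
- Control, m = 30: 0.1264×0.8736×1.58/210 = 0.000831.
- Intervention, m = 34: 0.28×0.72×1.66/238 = 0.001406.
- Standard error = √0.002237 = 0.0473, and 0.1536/0.0473 = 3.248.
- Power = Φ(3.248 − 1.960) = Φ(1.288) = 90.1%.

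With 33 per intervention centre, power is 89.8%, so 34 is the smallest size that reaches 90%. Then 7×30 + 7×34 = 448 and 448/0.9 = 497.8, rounded up to 498. Both figures reproduce exactly, so the arithmetic is sound. It leaves nothing over for patients outside the primary analysis.

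**Power when only a share f counts.** Replace 30 and 34 by 30f and 34f and keep everything else. For f = 50% (15 and 17 per centre):
- v1 = 0.11042×1.28/105 = 0.001346.
- v2 = 0.2016×1.32/119 = 0.002236.
- Standard error = 0.0599, and 0.1536/0.0599 = 2.566.
- Power = Φ(0.606) = 72.8%.

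The article does not give f, so the range below is assumed. The last column is the enrolment that would keep 448 evaluable patients, before and after the 10% loss (448/f and 498/f, rounded up).

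| Share newly diagnosed (assumed) | Evaluable of 448 | Power | Enrolment needed |
|---|---|---|---|
| 100% | 448 | 90.1% | 448 / 498 |
| 90% | 403 | 88.2% | 498 / 554 |
| 75% | 336 | 84.2% | 598 / 664 |
| 50% | 224 | 72.8% | 896 / 996 |
| 25% | 112 | 49.2% | 1792 / 1992 |
| 10% | 45 | 24.9% | 4480 / 4980 |

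The table keeps 12.64% and 28% as the proportions among newly diagnosed patients. That is a further assumption, because the 12.64% is quoted for patients with AF generally.

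**The case against.** The best defence is that newly diagnosed may be loose wording for the initial patients of the Interventions section. That group can include people with long-standing AF who have never been anticoagulated and are attending the centre for AF for the first time. The Background says that many patients go to superior hospitals or remain unmanaged, so the group could be most of those enrolled and the loss of power small: 88% at a share of 90%, 84% at 75%. This stands as a caution about size. It does not remove the conflict, because patients already on anticoagulants remain eligible, are not initial patients, and are still counted in 448.

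The restriction may also be deliberate. The decision scored in the Outcomes section (prescribe, refer or refrain) belongs to the initial pathway. Follow-up patients on a NOAC or on no anticoagulant are kept under follow-up, and those on warfarin get INR-based advice. This also stands, and it means that extending the outcome to everyone is not a free remedy.

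A reader might go further in three ways that the article does not support.
- That most enrolled patients fall outside the primary analysis: no share is given.
- That newly diagnosed patients could not be recruited in time. The Trial status section says "It is planned to enroll participants in Jan. 2022, and to follow up until Jan. 2023", which may mark only the start of enrolment, and its schedule figure is not shown. The 53 pilot patients in the Introduction describe how many were managed for over a year, not how fast they were recruited.
- That counting prescriptions rather than patients over-weights frequent attenders: nothing says that repeat prescriptions enter the denominator, and the definition reads naturally as one decision per patient.

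**Conclusion.** The mismatch is real and lies in what the article states, not in what it leaves out. The 90% power applies to 448 evaluable patients with AF. The primary analysis as defined covers an undefined, unquantified subset of them. For any share below 100%, power is below 90% under the plan's own inputs.

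The direction is certain, but the size is not. It runs from about two percentage points lost at a share of 90% to power of about one half at 25%, and the article does not say where in that range the trial lies. These figures use normal theory, the plan's proportions and ICC, and the same share in every centre. An analysis plan written later could not satisfy both sections without changing one of them, so the point should be settled before outcome data are examined.

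**What to change.** **Main route, keeping the restriction.** Define newly diagnosed, for example by tying it to the existing definition of initial patients. State that one decision per patient is scored. Then either say that 448/498 counts only patients evaluable for the primary outcome, or give the expected share and restate the power for that number. The wording costs nothing. If 448 evaluable patients are to be kept, the cost is the extra enrolment in the table: 996 instead of 498 at an assumed share of 50%.

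**Alternative, if all enrolled patients are meant.** Remove the restriction from the Outcomes section, state how agreement is scored for follow-up patients, and make newly diagnosed status a pre-specified subgroup. This needs no more patients, but patients whose management the tool would not change could dilute the effect. As an illustration, with all 448 counted and control at 12.64%, power falls to about 76% if the intervention proportion is 25% and to about 55% if it is 22%. Both proportions are assumptions.

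Either route is an amendment to the text. The choice should be recorded with its date, because the analysts are not blinded.

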**Methods:**

This study will be a prospective cluster randomized controlled trial, conducted among 14 community health centers in Shanghai which were randomized as the intervention group and control group in a ratio of 1:1. The intervention group will use the CDSS in the consultation of patients with AF and the control group will maintain their usual care. The trial will include 498 patients with AF and the follow-up period will be 12 months. The primary outcome is set as the proportion of antithrombotic treatment prescriptions in agreement with recommendations in the latest China’s AF-related guidelines. The secondary outcomes are the frequency of consultation, the compliance rate of international normalized ratio (INR) in patients with warfarin, stroke morbidity, treatment compliance, medication satisfaction, and the cost-benefit analysis. Per-protocol (PP) analysis and the intention-to-treat (ITT) analysis will be conducted.

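### The primary outcome is announced as agreement with guidelines but defined as agreement with the CDSS's own advice, with no scoring step stated for control patients and referral counted as success

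*Protocol article*

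**What the plan says.** The Outcomes section opens with this sentence: "The primary outcome is the proportion of antithrombotic treatment prescriptions, in agreement with recommendations in the AF guidelines". The Abstract agrees, giving "the proportion of antithrombotic treatment prescriptions in agreement with recommendations in the latest" Chinese AF guidelines. The next sentence of Outcomes turns this into a measurement. For newly diagnosed patients, it takes the agreement rate between the doctor's prescription "and the system’s recommendations, including prescribing anticoagulation drugs or recommending referral to superior hospitals for patients with anticoagulation indications", plus not anticoagulating patients who lack an indication or have a contraindication.

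Four other places bear on this definition:

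- Preparation: "the CDSS will be embedded into the HIS of community health centers in the intervention group". Control centres continue usual care (Abstract).
- Initial patients: the GP selects the ECG and echocardiography options and fills gaps in the record by asking the patient. Among the items considered is "medical history including initial AF", followed by several diseases, and then: "If the patients are diagnosed with any one of the diseases, the CDSS will advise referral".
- Blinding: "The researchers, participants, and data analysts will not be blinded".
- Sample size: the planning rates are 12.64% receiving appropriate anticoagulants and 28% with appropriate anticoagulation in the pilot intervention group. Referral is not mentioned.

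**The concern.** A reference standard should be independent of the intervention and obtained in the same way in both arms. Here the standard is the output of the intervention. An intervention GP sees the advice and is then scored on following it, so agreement partly measures uptake of the tool. If the tool departed from the guideline anywhere, following it would still score as correct.

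For a control patient no system recommendation arises in the consultation, and the article does not say who or what supplies one. If it is reconstructed later, it rests on records that were not completed under the tool's prompts, and nothing in the article masks the scorer to arm.

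The referral route raises a separate problem. The outcome is named for antithrombotic prescriptions, yet a recommendation to refer scores the same as a prescription, whether or not treatment follows. A positive result could then come from more anticoagulation, from more referral, or from both, and the single proportion would not show which.

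**Working it through.** **1. The definition, read side by side.** The headline comparator is the guideline. The operative comparator is "the agreement rate between the doctor’s anticoagulation prescriptions for newly diagnosed patients and the system’s recommendations". The second is introduced as the definition of the first, so it is the one an analyst would apply. The two coincide only if the system reproduces the guideline in every case and can be run on equal inputs in both arms. The Introduction subsection under Interventions supports the first condition in part: the CDSS is built on Chinese AF documents and its decisions were checked by cardiological experts. Nothing in the article addresses the second.

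**2. The referral route.** The text can be read as crediting referral for any patient with an indication, or only where the system itself advises referral. On either reading a success needs no prescription.

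**3. The plan's own sample size.** Inputs from Sample size: p1 = 0.1264, p2 = 0.28, ICC ρ = 0.02, two-sided α = 0.05, power 90%, k = 7 centres per arm, m1 = 30 per control centre. The article gives no formula. An unpooled two-proportion z test with a design effect in each arm reproduces the figure:

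SE² = p1(1−p1)[1+(m1−1)ρ]/(k·m1) + p2(1−p2)[1+(m2−1)ρ]/(k·m2); power = Φ((p2−p1)/SE − 1.96).

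- Control term: 0.1104 × 1.58 / 210 = 0.000831.
- Intervention term with m2 = 34: 0.2016 × 1.66 / 238 = 0.001406.
- SE = √0.002237 = 0.0473; 0.1536/0.0473 − 1.96 = 1.288; power = 0.901. With m2 = 33 power is 0.898, so 34 is the smallest size that reaches 90%.
- N = 7×30 + 7×34 = 448, and 448/0.9 = 497.8, rounded up to 498. Both figures match the article.

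The arithmetic is sound, but it is for rates of appropriate anticoagulation, not for the composite in Outcomes.

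**4. What referral alone could do.** Assumptions: anticoagulation stays at 12.64% in both arms, the composite starts from that value, and only referral agreement rises, by d, in the intervention arm. The same formula and cluster sizes apply.

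| d (points) | Intervention rate | SE | Power |
|---|---|---|---|
| 5 | 17.64% | 0.0429 | 0.213 |
| 10 | 22.64% | 0.0453 | 0.598 |
| 15.36 | 28.00% | 0.0473 | 0.901 |

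A referral-only shift of the planned size would be declared a benefit with about 90% probability, although anticoagulation had not changed. The documents give no value for d, so the rows show a range and are not a forecast.

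**The case against.** Several counter-arguments have force.

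- **Control patients can still be scored.** Preparation says where the tool is installed for use, not where its rules may be applied for scoring. Data collection and management describes questionnaires and health records without limiting them to one arm. A reader might infer that no reference can exist for control patients. The documents do not support that. They support only that no scoring step is stated and that inputs may be captured differently by arm. The condensed article may omit such a step, but it does fix the comparator as the system's advice.
- **The tool is a reasonable proxy.** It is guideline-based and expert-checked, and Outcomes lists criteria that could apply to either arm. No departure from the guideline is shown. This stands, but a proxy that is also the intervention is still not independent of it.
- **Referral is deliberate.** Objectives names the two-way referral system as an aim, and the tool advises referral in several situations. This stands, and it argues for keeping referral visible as a component rather than deleting it.

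Three stronger readings are tempting and should not be made.

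- A reader might infer from the Background that control GPs already refer widely and so would score as agreeing. That text describes patients seeking hospital care or remaining unmanaged. It does not describe GPs recommending referral.
- A reader might infer from the initial-AF wording that agreement reduces to referral. The term is undefined, its figure is not shown, and the same section goes on to scores and treatment suggestions for initial patients.
- A reader might calculate the share of non-concordant control patients whose referral would lift control agreement to 28%: 0.1536/0.8736 = 17.6%. That credits referral to patients without an indication. If only 80% have one (an assumption), the share is 0.1536/(0.80 × 0.8736) = 22.0%. No document gives a referral rate, and 12.64% is not baseline agreement because it omits correct withholding.

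**Conclusion.** The concern holds as a fault in the definition of the primary outcome. The article names one reference standard and fixes another. The one it fixes is the intervention's own output, with no common scoring procedure stated for the two arms and no masking. Counting referral as success means the composite can move without anticoagulation moving, and the sample size was calculated for anticoagulation alone.

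The direction of any net bias is not established. Following displayed advice and extra referral would favour the intervention, while referral by control GPs would dilute the difference. The size is illustrative: about 21%, 60% and 90% power for referral-only rises of 5, 10 and 15.36 points. These figures rest on a 12.64% starting point for the composite, which the documents do not give. A starting point nearer 50% would lower the power for the same rise.

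It would go too far to say the trial cannot answer its question. If the reference is redefined and the components are shown, it can.

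**What to change.** 1. Define the reference as named, dated guideline rules. Code them once and apply the script to the same minimum data set in both arms, with arm labels masked for scoring.
2. Do not use CDSS output generated in the consultation as the reference. Keep agreement with that output as a process measure in the intervention arm.
3. Beside the composite, report two components by arm: prescribing or withholding in line with the guideline, and referral. Whether referral stays in the primary composite is the sponsor's choice, given the referral aim. State when a referral counts.
4. In Sample size, state that 12.64% and 28% refer to anticoagulation and not to the composite that includes referral.
5. Reconcile the initial-AF referral text under Initial patients with the newly diagnosed population in Outcomes. This review takes no view on which referral rule is clinically right.

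The cost is protocol wording and one scoring script, with no change to allocation or recruitment. The downside is that records with missing inputs need one handling rule common to both arms, fixed before scoring starts. Control records may have more gaps, because GPs there have no prompt to fill them.
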